### Statistical analysis

The Statistical Package for the Social Sciences version 14.0 for Windows (SPSS Inc.) will be used. Group comparisons are based on intention-to-treat analysis. Non-parametric tests are used for comparisons of means within groups (Wilcoxon's Signed Ranks Test) and between groups (Mann-Whitney Test) if our expectation of a skewed distribution of Oxford and Harris Hip scores postoperatively is confirmed. Chi-square (Fisher's Exact) tests are employed for analyses of categorical variables. Cumulative implant survival is calculated by Kaplan-Meier time series (Mantel-Cox log rank test). A two-sided p-value of < 0.05 is assumed to be significant.

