### Measurements

In this study the following outcome parameters will be assessed: bone densitometry and serum metal ion concentration (primary outcome parameters), self reported functional status, physician reported functional status, range of motion, number of dislocations, radiographic evaluation and prosthetic survival (secondary outcome parameters). Measurements will take place preoperatively, perioperatively, and postoperatively (6 weeks, 1 year, 5 years and 10 years).

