#### Self-reported and physician reported functional status and range of motion

The validated Oxford self-rating questionnaire will be used to assess self reported functional status [10]. The validated Harris Hip Score is used to assess patient and physician reported functional status, as well as range of motion [11,12].

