### Sample size

It is our hypothesis that large head metal-on-metal arthroplasties will show less bone mineral density loss and higher serum metal ion concentrations compared to the conventional 28 mm metal-on-polyethylene articulations. In order to detect a least clinical relevant difference in bone mineral density (BMD) of 0.25 g/cm^2 ^with a standard deviation of 0.4, 41 patients are needed in each group (alpha 0.05, power 0.80). Based on previous work with cemented THA we expect a drop-out rate of 10%, but we also expect conversion to cemented cups if adequate cementless fixation fails. We therefore aim to include 50 patients in each group. Comparable studies also used 50 patients in each group [15,16]. In order to detect a clinical difference of 2.5 μg/liter in serum metal ion concentration with a standard deviation of 1.8, 8 patients per group are needed (alpha 0.05, power 0.80). To compensate for patients withdrawn from the study, (the first) 15 patients will be included in each group. A comparable study used 10 patients in each group [17].

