## Discussion

Superior results of large head metal-on-metal total hip arthroplasty over conventional hip arthroplasty have been put forward by experts, case series and the industry, but to our knowledge there is no randomized controlled evidence. This study will compare both arthroplasties. Periprosthetic bone density loss will be the main focus. In the short term we will be able to determine whether large head articulations increase clinical range of motion and reduce the number of dislocations. Furthermore, the trial will provide insight in short-term and long-term serum metal ion levels. A related research project will focus on the effects of metal ions on human osteoblast cells in vitro. This is important since the long-term risks of systemic metal ion exposure are unknown. Major pitfalls in orthopaedic surgery research have been the absence of a control group and the lack of randomization. This study overcomes both these drawbacks.

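### If the expected skew is confirmed, the only between-group test named for the Oxford and Harris scores cannot adjust for the preoperative score, so some precision is lost (minor; secondary outcomes)

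*Protocol article*

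**What the plan says.** **Timing.** The Measurements section of the protocol article sets one schedule for all outcomes: "Measurements will take place preoperatively, perioperatively, and postoperatively (6 weeks, 1 year, 5 years and 10 years"). It makes no exception for the functional scores, so a preoperative Oxford and Harris score is planned.

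**Status.** The same section lists "self reported functional status, physician reported functional status, range of motion, number of dislocations, radiographic evaluation and prosthetic survival (secondary outcome parameters"). No sample size or power is given for function or motion.

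**Instruments.** Self-reported function is measured with the Oxford questionnaire. For the rest, "The validated Harris Hip Score is used to assess patient and physician reported functional status, as well as range of motion".

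**Tests.** The Statistical analysis section says: "Non-parametric tests are used for comparisons of means within groups (Wilcoxon's Signed Ranks Test) and between groups (Mann-Whitney Test"). The sentence goes on with a condition: "if our expectation of a skewed distribution of Oxford and Harris Hip scores postoperatively is confirmed". The section names no test for the case without skew, no baseline covariate and no adjusted model. On significance: "A two-sided p-value of < 0.05 is assumed to be significant".

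**Claims.** The Background expects function to be equal in the two arms and motion to be greater with metal-on-metal. The Discussion adds: "In the short term we will be able to determine whether large head articulations increase clinical range of motion".

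**The concern.** The preoperative score will be available for each patient and is likely to predict the postoperative score to some degree. The one named test that naturally uses it is the within-group Wilcoxon test. That test shows whether hips change after surgery in each arm, which is not the question the trial was randomised to answer. The named comparison of the implants is a rank test with no place for a covariate.

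The functional comparisons have no planned power, because the trial was sized on bone density and metal ions. The article nonetheless expects equal function, and a non-significant Mann-Whitney p-value is weak support for equality. A narrower interval around an adjusted difference would say more, from data that are already to be collected.

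**Working it through.** **1. The plan's own figure.** The Sample size section begins: "In order to detect a least clinical relevant difference in bone mineral density (BMD) of 0.25 g/cm^2". It assumes SD 0.4, alpha 0.05 and power 0.80.

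n per arm = 2 × [SD × (1.960 + 0.842) / difference]² = 2 × [0.4 × 2.802 / 0.25]² = 40.2, rounded up to 41.

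This agrees with the stated 41. It concerns bone density; there is no corresponding figure for function.

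**2. Inputs for the functional comparison.**
- From the article: 50 per arm and 10% drop-out, so 50 × 0.90 = 45 evaluable per arm; two-sided alpha 0.05.
- Assumed, because the article gives neither: a true difference of 0.5 SD, and a pre-to-post correlation rho between 0.2 and 0.7.

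**3. Formulas.** Take equal SDs before and after surgery, and express each analysis as an effective standardised difference:
- postoperative values only: 0.5
- change from baseline: 0.5 / √[2(1 − rho)]
- baseline-adjusted (ANCOVA): 0.5 / √(1 − rho²)

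At rho 0.5, for example, the adjusted value is 0.5 / √0.75 = 0.577 and the change-score value is 0.5 / √1 = 0.5.

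**4. Two-sample t-test power at 45 per arm.**

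| rho | Variance saved (rho²) | Postoperative only | Change score | Adjusted |
|---|---|---|---|---|
| 0.2 | 4% | 0.65 | 0.46 | 0.67 |
| 0.3 | 9% | 0.65 | 0.51 | 0.69 |
| 0.5 | 25% | 0.65 | 0.65 | 0.77 |
| 0.7 | 49% | 0.65 | 0.86 | 0.91 |

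The normal approximation runs about one point higher: 0.66 unadjusted, and 0.68, 0.70, 0.78 and 0.91 adjusted. It puts Mann-Whitney on normally distributed postoperative values at about 0.64. On either scale the gain from adjustment is about 2 points at rho 0.2, 4 at 0.3, 12 at 0.5 and 25 at 0.7.

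**5. Detectable difference at 80% power (t-test).** It is 0.597 SD unadjusted. Multiplying by √(1 − rho²) gives 0.585 SD at rho 0.2, 0.570 at 0.3 and 0.517 at 0.5. At rho 0.5 the confidence interval is 1 − √0.75 = 13% narrower.

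**6. Does this carry over to skewed scores and rank methods?** A simulation used 45 per arm, a latent difference of 0.5 SD, a ceiling on the postoperative score and 3,000 runs per setting:

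| rho | Mann-Whitney, postoperative | Rank ANCOVA |
|---|---|---|
| 0 | 0.60 | 0.59 |
| 0.2 | 0.56 | 0.57 |
| 0.3 | 0.59 | 0.63 |
| 0.5 | 0.57 | 0.67 |
| 0.7 | 0.58 | 0.81 |

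The Mann-Whitney column does not depend on rho, so its spread is simulation error (standard error about 0.009). The pattern matches step 4: little or nothing at low correlation, a clear gain from about 0.5 upwards, and no material loss if baseline is uninformative.

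**The case against.** The case for leaving the text alone has several parts.

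- **The rank test is conditional.** This stands: Mann-Whitney applies only if skew is confirmed, and the article does not exclude an adjusted model otherwise. Skew is, however, what the authors expect, so Mann-Whitney is their anticipated analysis.
- **Baseline may not be discarded.** A reader might infer that Mann-Whitney is run on postoperative values and ignores the preoperative score. The text does not establish that. The word for after surgery describes the distribution expected to be skewed, and a rank test on changes from baseline is not excluded. The recommendation survives either reading, because adjustment has more power than change scores at every rho in the table, and change scores do worse than postoperative values alone when rho is below 0.5.
- **Range of motion is not covered.** A reader might extend the rule to motion. The skew condition names only the Oxford and Harris scores. Motion is listed as a separate outcome, although it is collected through the Harris assessment, and no test is explicitly tied to it.
- **The unadjusted comparison is valid.** This stands. Allocation is randomised and concealed, and analysis is by intention to treat. A reader might infer that chance imbalance in preoperative function would bias the result; the test's error rate already allows for such imbalance, and the cost is precision.
- **A condensed article may leave covariates to a fuller plan.** This has weight for a missing detail. Here the article does name a between-group test, and a fuller plan would have to replace that test in order to adjust.
- **The size is assumed.** This also stands. At rho 0.3 or less the gain is 4 points or fewer.

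**Conclusion.** The point holds as a minor one. If the expected skew is confirmed, the only between-group test named for the Oxford and Harris scores cannot adjust for the preoperative value. The article leaves open which values are compared and which test applies to range of motion.

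The consequence is lost efficiency in secondary comparisons. The direction is secure whenever baseline predicts outcome. The size rests on an assumed 0.5 SD difference, 45 evaluable patients per arm and a correlation that the article does not give; it runs from negligible at rho 0.2 to about 12 power points at rho 0.5. The documents do not support a claim of bias, and the bone density and metal ion comparisons are not affected by this point.

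**What to change.** In the Statistical analysis section:

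- Compare postoperative Oxford and Harris scores between arms with a model that includes the preoperative value: ANCOVA, or rank ANCOVA or a proportional-odds model if the scores are skewed as expected.
- Apply the same approach to range of motion, and name it there, since no test is tied to it now.
- Report the adjusted effect with a 95% CI. Rank ANCOVA gives a p-value but no difference on the score's own scale, so if it is used, take the estimate and interval from ANCOVA or the proportional-odds model.
- Keep the within-group Wilcoxon tests as description, not as evidence about the implants.

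The cost is wording and one model parameter per comparison. No extra patients, visits or measurements are needed, and SPSS fits these models. A short statement on patients without a preoperative score would be needed.

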## Discussion

Superior results of large head metal-on-metal total hip arthroplasty over conventional hip arthroplasty have been put forward by experts, case series and the industry, but to our knowledge there is no randomized controlled evidence. This study will compare both arthroplasties. Periprosthetic bone density loss will be the main focus. In the short term we will be able to determine whether large head articulations increase clinical range of motion and reduce the number of dislocations. Furthermore, the trial will provide insight in short-term and long-term serum metal ion levels. A related research project will focus on the effects of metal ions on human osteoblast cells in vitro. This is important since the long-term risks of systemic metal ion exposure are unknown. Major pitfalls in orthopaedic surgery research have been the absence of a control group and the lack of randomization. This study overcomes both these drawbacks.

## Conclusion

This randomized controlled study has been designed to test whether large head metal-on-metal cementless total hip arthroplasty leads to less periprosthetic bone density loss and higher serum metal ion concentrations compared to 28 mm metal-on-polyethylene cementless total hip arthroplasty.
